## Innovative impact

The results of PREVENTCD may have an innovative impact in the European Food Industry, concerning the scientific basis for the composition of bottle-feeding, aimed

to prevent CD in children in whom breast-feeding is not possible. In this context, the studies on gluten content in breast-feeding samples from mothers from high risk families from different European countries with different nutritional practices, will offer novel data to the European Industry in its effort to develop food for health. Moreover, the *commercial diagnostic tools* used in PREVENTCD, i.e. serological markers for CD (AtTG, AGA) and autoimmunity (TPO), and also for determining the genetic vulnerability (HLA-typing) for CD, will have a *marketing advantage* as being used in high quality international research.

### 5.1 Contributions to standards

European and national guidelines for gluten introduction into the diet of infants have been changed several times over the years, and in retrospect the scientific evidence behind some of these changes can be questioned. In fact, the European infants of today get an introduction to gluten containing foods following guidelines that, for the most part, are not based on scientific evidence and the option for primary prevention of CD is not properly taken care off. The large majority of the European infants get relatively big quantities of gluten introduced at once after the age of 6 months, a moment when very few of them are still breast-fed. Thus, ***new European guidelines for infant feeding with respect to introduction of gluten-containing foods are needed***, and should be based on high quality scientific evidence. The PREVENTCD project will provide such evidence through *multidisciplinary research collaboration across Europe*. A better understanding of the influence of the dietary history on human health will establish the basis to provide safer, and health-promoting early nutrition guidelines to improve the health and well being of the European citizens. If the PREVENTCD hypothesis concerning the possibility of induction of tolerance for gluten in children is proven to be correct, we will develop new *European guidelines of early nutrition, concerning gluten introduction and breast-feeding*, to achieve primary CD prevention in the general population and, particular, in children from high-risk families for CD. The new European guidelines will be developed and disseminated in collaboration with the Committee of Nutrition of the European Society for Paediatric Gastroenterology, Hepatology and Nutrition (ESPGHAN).

### 5.2 Contribution to policy developments

In Europe, CD has been on the scientific agenda since the 1950's, however, increasingly so during the last twenty years. In comparison, in U.S and globally CD

has only recently been recognized as a frequent health problem. By PREVENTCD the *European researchers* within their respective field, and the industry involved, *will keep and strengthen the leading role of Europe in the frontline of CD research worldwide*. Success within this research area can only be reached by an *integrated European research effort*, taking advantage of all the currently available European knowledge and know-how with the large range of disciplines involved. Moreover the participation of the large number of families with CD necessary to carry out the study is only possible by collaboration among European countries with well-organized Coeliac Patients Societies. In this context the participation of the Association of European Coeliac Disease Societies (AOECS) is highly valuable. In addition, the “experiment in nature” that has taken place in Sweden during and after national changes in early gluten consumption, offers a unique opportunity to study the effect of these changes in the primary prevention of CD in one big population of European pre-adolescents.

The PREVENTCD partners are well established in the scientific community within their own countries, and also have international networks across Europe as well as globally. The Dutch partnership includes leaders of the Dutch Coeliac Disease Consortium (CDC), a project supported by the Dutch Government, which brings together partners from industry, patient community and Dutch knowledge-based institutions, to develop the scientific bases for safer foods and for effective diagnosis, prevention and therapy of CD. The coordinator of PREVENTCD, [name], and several of the partners ([name], [name], and [name]) are responsible for the EU funded project CDEUSSA (Food – CT- 2005- 517787) aiming, a.o., to create a *European platform for future research on prevention and effective treatment of CD by a multidisciplinary approach to integrate basic scientific knowledge in clinical applications and food industry*. This European platform offers an excellent opportunity to bring new knowledge into the project and will act as its Advisory Board.

### **5.3 Risk assessment and related communication strategy**

WP1: the management and governance structure of PREVENTCD is described in detail, including the risks and contingency plans, under "6.1 Project management".

WP2: no contingencies or risks are expected.

WP3: the main activity in WP3 is represented by the recruitment of newborns belonging to at-risk families for CD. The number of newborns expected from each participating group has been carefully evaluated on the basis of the number of families followed-up in that group and of the birth rate of the local general population.

Deliverables set at the end of each year of the project will allow following strictly the progression of the recruitment. Already at month 12 it will be possible to have a first evaluation of the recruitment. If at this moment it turns that the recruitment of newborns is significantly lower than expected, all efforts will be done to increase the recruitment rate. This will mainly be done by increasing the awareness about the project by, among others, the members of the local Coeliac Patients Associations. Reinforcement of the call to participate may be done by additional information on the Journals and web-sites of the AOECS and local associations, as well as on the local newspapers and radio and television programmes. Those strategies have previously proved to be successful in increasing the participating rate by target groups in research projects.

Although the project clearly states that breast feeding will be strongly encouraged for all the participating children, and it is expected that families with coeliac cases will strictly comply with this prescription, it is possible that a proportion of infants at the age of 4 months will turn out not to be breast fed. To avoid bias they will be in any case enrolled. Retrospectively, the impact of the length of breast feeding on the outcome of the intervention will be evaluated. It must be emphasised that no evident risk are foreseen for deliverable 3.1, which may be considered as one of the most important deliverables of the whole project. This project is the first large prospective study that will describe the natural history and the development of the specific immune response of subjects belonging to "at-risk" families, in relation to a very precisely defined genetic background. It is also important to stress that the work planned in two other important WPs (genetics and immunology) although certainly done on the infants recruited in WP3 and WP4, are not strictly dependent on the deliverables 3.4, 3.5 and 3.6.

WP4: the population based study doesn't involve any intervention with respect to infant feeding, but takes advantage of a previous "experiment" in Sweden with extensive changes with respect to breast-feeding and early gluten exposure. Thus, for WP 4 risks no contingencies or risks are expected.

WP5: this part of the project relies on existing knowledge on the genetics of CD and the technology available for high-throughput genotyping. This implies that the feasibility is good. The genotyping will be performed on an Illumina platform which is an extremely powerful technology currently in use by numerous groups and also fully operational the UMCG. No contingencies or risks are expected to execute this WP.

WP6:

*Gluten analysis*

Characterization of the gluten preparation will be done with T cell reagents already established by partners 1 and 13 and with monoclonal antibodies established by partner 1. These tests have already proved to yield reliable results. We therefore see no risks associated with this part of the work package.

*Breast milk analysis*

For the breast milk analysis we will primarily use the monoclonal antibody based assays. In a pilot study performed in the Netherlands our preliminary findings indicate that gliadin fragments can be reliably detected in the breast milk samples and that these levels remain stable over extended periods of breast milk feeding. We therefore see no risks associated with this part of the work package.

*Detection of gluten specific T cells HLA tetramers during gluten exposure.*

Detection of gluten specific T cells in peripheral blood by HLA tetramers has so far been successfully undertaken in adult coeliacs in remission on day 6 after a 3 day oral gluten challenge. Detection of HLA tetramer positive T cells has so far not been tested in children and it is unclear whether gluten reactive T cells can be detected in peripheral blood when CD is about to precipitate. The amount of blood needed to detect tetramer positive T cells in children is also uncertain because there is no data

available on the frequency of gluten reactive T cells in peripheral blood under these conditions. Initially we will therefore test 10 patients for tetramer staining. If no positive results emerge, we will terminate this approach and explore alternatives, in particular ELIspot analysis of peripheral blood samples or CFSE dilution experiments in which responding T cells are visualized by the CFSE dilution as the results of cell division. Again we will test 10 patients in each group. If all approaches fail, this part of the workpackage will be terminated.

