Epidemiological studies from Sweden suggest that early nutrition patterns may have a significant impact on the later risk of developing CD. The occurrence of "epidemics" of CD after changes in the Swedish infant feeding during the 1980s and 1990s, suggests that the disease may be preventable by improving early nutrition and inducing tolerance to gluten in predisposed individuals. The leader of Swedish research, [name], who is a partner of the proposed STREP, has shown that ongoing breast-feeding during the period of gradual introduction of gluten containing foods into the infant diet reduces the risk of symptomatic CD (24,25). Based on an estimate of the attributable fraction, *half of the CD cases during the Swedish epidemic might have been avoided* if all infants had been introduced to gluten in small amounts while still being breast-fed. The latter finding opens the way to possible prevention strategies, but they are in conflict with the actual European guide lines for infant nutrition. This advice is to introduce gluten into the diet no earlier than at the age of 6 months (26). At this age, only a low percentage of the European children, ranging from 1-46% in the different European countries, receive breast-feeding (27). On the other hand, the Swedish study only investigated the effect of the early dietary history on symptomatic CD in children aged 2. It may be that the nutritional factors only have an effect on the symptoms of CD and/or on the time of presentations of the symptoms. In addition, there is no information on the biological mechanisms involved in the effect of early nutrition in the development of CD.

Basic science, including genetics, immunology and genomics, should find its way into the clinical application in the prevention of CD. *The objective of this STREP is to close the gap between basic science knowledge, concerning genomics and immunology, and its applications in the prevention of CD, concerning nutrition history, medicine, Public Health and food industry.*

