**Introduction**

We will carefully assess the early immune response to gluten in 1.000 infants from high-risk families for CD from different European countries and with different degrees of genetic predisposition for the disease, under different nutritional conditions, including gluten introduction, gluten exposure and breast-feeding practices.

- Design: double blind prospective randomised food intervention study. During the start-up period of the project, due to delay in obtaining the gluten preparation for the intervention on time, after informed consent of their parents-guardians, the recruited children received placebo in a non-randomised, open way.
- Invitation to participate: the families will be invited to participate by the Association of European Coeliac Disease Societies (AOECS) ([www.aoecs.org](http://www.aoecs.org)) or by local Coeliac Disease Societies. The CD Societies from the Netherlands (NCV) ([www.coeliakievereniging.nl](http://www.coeliakievereniging.nl)); Campania, Italy ([www.rcm.napoli.it/celiachia](http://www.rcm.napoli.it/celiachia)); Madrid (SCM) ([www.celiacosmadrid.org](http://www.celiacosmadrid.org)), Valencia (ACECOVA), Catalonia (SMAP) ([www.celiacscatalunya.org](http://www.celiacscatalunya.org)), Spain; Israel (CAI), Poland (PCS), Croatia, Hungary ([www.coeliac.hu](http://www.coeliac.hu)) and Germany ([www.dzg-online.de](http://www.dzg-online.de)) will invite their members with CD expecting a newborn (child or sibling) during the next 18 months to participate. Partner 9, the AOECS, is able to easily link the project to each country in Europe, in particular those member states with large populations, in order to ensure the necessary number of infants. (table 2).
- Informed consent: during pregnancy, the families will be asked informed consent for participation by the local responsible physician.
- Enrolment: after informed consent is given, the families will be enrolled in the study. Breast-feeding during at least six months will be STRONGLY encouraged to all the families.
- Genetic risk stratification: the genetic risk for CD will be assessed and stratified as described in WP 5 “Genetics”.
- Randomisation to "tolerance induction for gluten" or to the "control" group. Shortly before the dietary intervention, the children bearing HLA-DQ2 and/or

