### Objectives

Assessment of the possibilities to achieve primary prevention for CD in genetically predisposed children by early dietary intervention consisting of introduction of small quantities of gluten during the period of breast-feeding

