### Description of work

- Assessment of the early immune response to gluten in approximately 1000 infants from high-risk families for CD from different European countries. The families will be invited to participate, among others, by the local Coeliac Disease Societies in collaboration with the Association of European Coeliac Disease Societies (AOECS). The CD Societies from the Netherlands (NCV)

([www.coeliakievereniging.nl](http://www.coeliakievereniging.nl)); Campania, Italy ([www.rcm.napoli.it/celiachia](http://www.rcm.napoli.it/celiachia)); Madrid (SCM) ([www.celiacosmadrid.org](http://www.celiacosmadrid.org)), Valencia (ACECOVA), Catalonia (SMAP) ([www.celiacscatalunya.org](http://www.celiacscatalunya.org)), Spain; Israel (CAI), Poland (PCS), Croatia, Hungary ([www.coeliac.hu](http://www.coeliac.hu)) and Germany ([www.dzg-online.de](http://www.dzg-online.de)) will collaborate in the study.

- The Societies will invite to participate their members with CD expecting a newborn (child or sibling) during the next 18 months. Informed consent to participate will be asked from the families by the local responsible physician.
- The children bearing HLA-DQ2 and/or DQ8 will be blindly randomised to either a group for "tolerance induction for gluten" or to a "control" group. At least 6 months of breast-feeding will be STRONGLY encouraged for all the children. At the age of 4 months tolerance induction will be attempted by the daily intake of 1g wheat flour (100 mg gliadin) during 8 weeks while continuing breast-feeding. No gluten will be given in these 8 weeks to control infants, but 1g. lactose as a placebo intervention. Danone will provide the placebo (lactose, Pharmatose) and the intervention product (Glutival obtained from Cargill). Danone has outsourced the production of the sachets with the gluten intervention / placebo products to NIZO Food Research, Ede, the Netherlands. NIZO will prepare and package the gluten intervention product as well as the placebo according to quality criteria adequate for infants aged 4-6 months. Every intervention sachet will be filled 1.8 gr Pharmatose and 0.2 gr Glutival (gluten intervention product); the placebo sachets will be filled with 2 gr of Pharmatose.  

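### The trial's one named breast-feeding analysis uses total length, partly settled after randomisation, although the hypothesis turns on whether breast-feeding is ongoing when gluten starts

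*Protocol*

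**What the plan says.** The WP3 objective (section 7.6) is prevention through "early dietary intervention consisting of introduction of small quantities of gluten during the period of breast-feeding". The WP3 description of work has the sachets taken daily "during 8 weeks while continuing breast-feeding".

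Section 5.3, under WP3, allows that "it is possible that a proportion of infants at the age of 4 months will turn out not to be breast fed". It continues: "To avoid bias they will be in any case enrolled". The analysis it then names is: "Retrospectively, the impact of the length of breast feeding on the outcome of the intervention will be evaluated".

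The WP3 introduction places randomisation just ahead of the intervention. Table 1 marks it at month 3, with the intervention at month 4 and a food questionnaire at birth and every month through month 12. The nutritional assessment paragraph says these questionnaires record breast-feeding. At least six months of breast-feeding is strongly encouraged for all families.

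The power analysis assumes 10% coeliac disease, a 50% reduction, 80% power and a two-sided 5% test, giving 474 per arm. It does not mention breast-feeding. The protocol names no stratification factor, subgroup or interaction term based on breast-feeding at the start of the intervention. Deliverable D3.1 promises a databank on gluten intake and breast-feeding but defines no analysis.

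**The concern.** Two exposures are being run together. One is whether the child was breast-fed when gluten began, which is what the hypothesis is about. The other is how long breast-feeding lasted in total. The protocol separates them itself. Section 9.3, discussing the Swedish epidemic, identifies ongoing breast-feeding at the time of gluten introduction, together with the amount of gluten, as the suspected cause. Section 2.1 reports breast-feeding during introduction and its duration as two distinct associations.

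The analysis named for the trial uses the second. For a child still breast-fed at month 3, total length lies in the future. It could be influenced by early symptoms or by reactions to the sachets. Groups formed on such a variable need not be comparable between arms, so a difference in treatment effect between short and long breast-feeding could be produced partly by the grouping. The finding most directly tied to the hypothesis would then rest on the weaker comparison, although a baseline variable free of this problem is available.

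**Working it through.** **1. When each candidate modifier is fixed**

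| Infant at randomisation (month 3) | Status before first sachet (month 4) | Total length |
|---|---|---|
| Already weaned | Known, no | Known, under about 3 months |
| Still breast-fed | Known once the last questionnaire before the sachets is in | Not yet known; fixed later |

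Length is therefore a baseline variable for the first row only. Status, taken from the last questionnaire before the first sachet, precedes any exposure in both rows.

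**2. The plan's own sample size**

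Inputs from the WP3 power analysis: p1 = 0.10, p2 = 0.05, two-sided 5% (z = 1.960), 80% power (z = 0.842), mean p = 0.075.

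- Uncorrected: n = [1.960·√(2·0.075·0.925) + 0.842·√(0.10·0.90 + 0.05·0.95)]² / 0.05² = 434.4, rounded up to 435.
- With continuity correction: n' = (434.4/4)·[1 + √(1 + 4/(434.4·0.05))]² = 473.6, rounded up to 474.

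The stated 474 reproduces exactly.

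**3. Sensitivity of all-randomised power**

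The share f not breast-fed at the start is not given in the protocol, so 10%, 20% and 30% are assumed. The model also assumes 10% risk whatever the feeding, a 50% reduction in breast-fed infants, and none in the others.

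- Intervention-arm risk: p2(f) = 0.10·[1 − 0.5·(1 − f)]
- Power = Φ{[d − c − 1.960·√(2·p̄(1 − p̄)/474)] / √([p1(1 − p1) + p2(1 − p2)]/474)}, where d = p1 − p2, p̄ is their mean, and c = 1/474 with continuity correction or 0 without.

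Worked for f = 0.20: p2 = 0.06 and d = 0.04. The critical term is 0.03454 and the standard error 0.01757. Uncorrected: (0.04 − 0.03454)/0.01757 = 0.311, power 62%. Corrected: (0.04 − 0.00211 − 0.03454)/0.01757 = 0.191, power 58%.

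| f | p2 | Relative risk | Power, corrected to uncorrected |
|---|---|---|---|
| 0 | 0.050 | 0.50 | 80-83% |
| 10% | 0.055 | 0.55 | 70-74% |
| 20% | 0.060 | 0.60 | 58-62% |
| 30% | 0.065 | 0.65 | 45-50% |

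**4. What the proposed analysis can deliver**

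Under the same model, with 474·(1 − f) breast-fed infants per arm, the comparison within that stratum has 75-79%, 70-74% and 63-69% power at f = 10%, 20% and 30%.

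The arm-by-status interaction is weaker. On the risk-difference scale its standard error is √[(0.09 + 0.0475)/(474(1 − f)) + 0.18/(474f)]. At f = 20% this is 0.0476, so power = Φ(0.05/0.0476 − 1.96), about 18%. Over f = 10-30% the power is 12-23% on this scale and 17-32% on the log odds ratio scale.

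**The case against.** The strongest reply is that one sentence in a project-risk section fixes no model or cut-point and does not exclude an analysis by status, which a statistical analysis plan (not available here) could add. That is fair as far as it goes. But the protocol does not leave the modifier open: it names length, and that choice can be judged as written.

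Second, length contains status: cutting it at about 4 months gives nearly the same yes/no variable. Blinding also limits differential weaning, and nothing in the protocol shows that symptoms drive weaning. All this stands. It makes the problem partial, confined to variation after randomisation.

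Third, length carries information of its own. A child weaned soon after the first sachet counts as breast-fed at the start but was not breast-fed for most of the 8 weeks, and the protocol cites evidence on duration. This is a good reason to keep length as an exploratory analysis.

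A reader might go further and infer any of the following, which the protocol does not support:

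- **That the sample size is wrong or the trial underpowered.** The 474 is correct on its inputs. The power loss needs zero effect without breast-feeding, which the protocol does not assert: the WP3 introduction also relies on an age window and cites a cohort that discounted breast-feeding, and section 9.3 invokes low-dose tolerance and treats breast-feeding as raising the chance of tolerance.
- **That at most 46% would be breast-fed.** The statement in section 2.1, "only a low percentage of the European children, ranging from 1-46% in the different European countries, receive breast-feeding", refers to 6 months of age in general populations. It does not describe 4-month-olds in coeliac families who are urged to breast-feed.
- **That enrolling non-breast-fed infants is a flaw.** It is sound for the all-randomised comparison.
- **That an analysis by baseline status should become the test of the hypothesis.** Its interaction is too imprecise for that.

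**Conclusion.** The point holds in limited form. The protocol chooses a breast-feeding modifier that is partly determined after randomisation, when a baseline modifier closer to its hypothesis is already being collected. The fault affects the breast-feeding analysis. The primary all-randomised comparison and the stated sample size are unaffected.

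The size of any bias from using length cannot be calculated from the protocol. The power figures for 10-30% not breast-fed rest on assumed shares and on benefit confined to breast-fed infants. They show how much could depend on that share and are not a forecast.

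**What to change.** - Keep the comparison of all randomised children as primary.
- Define breast-feeding status (yes/no) from the last food questionnaire before the first sachet, and pre-specify it as the effect modifier.
- Report the treatment effect in each status group with the arm-by-status interaction, described in advance as supportive and low-powered.
- Use status as an adjustment covariate. The randomisation need not change.
- Keep the analysis by length as exploratory, labelled as using a post-randomisation variable.
- Add the power sensitivity for a stated range of non-breast-fed shares, with its assumptions.

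The cost is analysis wording, since the questionnaires already supply the data. The drawback is imprecision: the breast-fed stratum is smaller than the whole trial, and a non-significant interaction must not be read as showing that breast-feeding makes no difference.
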